## Abstract

**Background:**

Attention-deficit/hyperactivity disorder (ADHD) is a prevalent neurodevelopmental condition affecting approximately 7% to 8% of children and adolescents, characterized by persistent inattention, hyperactivity, and impulsivity. Adolescence represents a period of heightened vulnerability, during which pharmacological treatments are frequently limited by adverse effects, suboptimal adherence, and partial response. Physical exercise, particularly high-intensity interval training (HIIT), has demonstrated superior effects on inhibitory control and inattention compared with moderate-intensity continuous exercise. However, the repetitive nature and high perceived exertion of traditional HIIT protocols result in poor adherence, especially in individuals with ADHD. Virtual reality (VR)–based exergames have been proposed as a strategy to sustain vigorous physiological demands while maintaining intrinsic motivation. Despite this potential, the existing literature is predominantly limited by passive control conditions, which prevent adequate control for the effects of VR immersion and cognitive engagement, limiting causal inference regarding the specific contribution of physiological exertion.

**Objective:**

This paper presents the protocol for a randomized clinical trial designed to evaluate whether an HIIT-based VR exergame produces greater improvements in inhibitory control and inattention symptoms compared with an active, nonexercise VR control condition in adolescents with ADHD.

**Methods:**

This multisite, parallel-group, single-blind randomized clinical trial will recruit 98 adolescents aged 12 to 17 years with a confirmed diagnosis of ADHD according to the *Diagnostic and Statistical Manual of Mental Disorders, Fifth Edition*, from 2 outpatient centers in Brazil. Participants will be allocated 1:1 to an HIIT-based VR exergame intervention (Move Sapiens) or an active control condition using the same VR platform without vigorous physical exertion. The intervention comprises 20 sessions over 4 weeks delivered in a home-based format following supervised laboratory familiarization. Primary outcomes are Swanson, Nolan, and Pelham Rating Scale version IV inattention subscale scores and go/no-go commission errors. Secondary outcomes include working memory, cognitive flexibility, processing speed, impulsivity, sleep quality, and anxiety symptoms. Analyses will follow an intention-to-treat approach using linear mixed-effects models.

**Results:**

The trial is ongoing. Funding was granted in October 2024. As of April 2026, 58 participants have been enrolled across 2 sites, of whom 46 (79.3%) have completed the full intervention protocol. Data collection is expected to be completed by October 2026, with results anticipated by December 2026.

**Conclusions:**

This trial will provide controlled evidence on the efficacy of an HIIT-based VR exergame for adolescents with ADHD using an active control condition matched for technological immersion. The design will enable examination of whether vigorous physical exertion beyond VR immersion and digital engagement constitutes an essential active component for improvements in inhibitory control and inattention in this population. If effective, the intervention may offer an engaging, home-based adjunctive treatment option for adolescents with ADHD.

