### Interventions

#### Intervention Group (HIIT-Based VR Exergame)

Participants allocated to the intervention arm will engage with Move Sapiens, a VR exergame developed using Unreal Engine (version 4.27; Epic Games) and delivered through the stand-alone Meta Quest 2 and 3S headsets (Reality Labs). The game provides a fully immersive, first-person experience where players operate a virtual exoskeleton to combat an autonomous drone. The mechanics require users to simultaneously strike the drone to deplete its health, avoid incoming attacks, and continuously adjust their motor responses. This design integrates rapid motor execution, sustained attention, inhibitory control, and visuomotor coordination. The protocol consists of 20 sessions delivered over a 4-week period (5 sessions per week). Each session lasts 7 minutes and 12 seconds, adhering to a structured HIIT format composed of 12 cycles. Each cycle comprises 16 seconds of maximal physical effort followed by 20 seconds of active recovery. This specific HIIT configuration was previously validated in a pilot crossover study [11]. Results demonstrated that this protocol elicits vigorous physiological responses (mean heart rate of approximately 161 beats per minute; peak heart rate of approximately 182 beats per minute) and significant metabolic stress (lactate accumulation) while maintaining high levels of intrinsic motivation and enjoyment, supporting its utility as a potent physiological stimulus. The structure and visual interface of the Move Sapiens VR exergame are illustrated in Figure 1.

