#### Control Condition (Nonexercise VR)

Participants assigned to the control group will use an adapted nonexercise version of Move Sapiens. This version preserves the same immersive VR environment, visual assets, and sound design but removes all components of physical exertion. Interaction occurs exclusively through a joystick. Session duration and frequency mirror those of the intervention group. This design enables examination of the specific contribution of vigorous physical exertion to the observed outcomes while controlling for VR immersion and digital engagement, both of which are preserved across conditions.

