Several limitations should be acknowledged. The single-blind design introduces the possibility of expectancy effects; however, this risk is partially mitigated by the use of an engaging active control condition matched for novelty and immersion. Notably, expectancy bias may disproportionately affect the parent-reported inattention outcome given that parents are aware of their children’s group assignment. The inclusion of the go/no-go task as a co–primary objective performance measure allows for a complementary assessment that is less susceptible to expectancy effects as it is independent of rater expectations. Furthermore, the 2 study arms differ not only in metabolic load but also in gross motor demand and task experience as the intervention requires full-body movement whereas the control condition involves joystick-only interaction. These differences are inherent to ecologically valid comparisons of this nature and preclude definitive attribution of any observed effects to a single component of the intervention. The 4-week intervention period may be insufficient to induce durable neuroplastic changes or sustained behavioral adaptations as longer intervention durations have been associated with stronger consolidation of executive function gains in meta-analytic studies. Nevertheless, budgetary and logistical constraints limited the feasibility of implementing longer protocols, and the selected intervention length is consistent with the duration most commonly used in studies evaluating HIIT, neuromodulation, and computerized cognitive training for ADHD [27]. Excluding participants currently receiving pharmacological treatment limits generalizability but was necessary to isolate the specific effects of the exercise intervention. Although parent-reported inattention outcomes may be subject to rater bias, this limitation is offset by the inclusion of objective, performance-based measures of inhibitory control, which have demonstrated sensitivity to high-intensity exercise interventions. Finally, while home-based delivery precludes direct supervision, structured remote monitoring provides systematic indexes of adherence and training intensity, thereby ensuring intervention fidelity.

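### Two VR arms give one contrast, the full-body HIIT exergame as a package against joystick VR, so the statements on the role of exertion and on an exertion-by-VR interaction claim more than the design can give

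*Protocol article*

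**What the plan says.** Three places in the protocol article describe what the design can show about exertion.

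- **Abstract, Conclusions.** The design is said to permit examination of "whether vigorous physical exertion beyond VR immersion and digital engagement constitutes an essential active component for improvements in inhibitory control and inattention".
- **Control Condition (Nonexercise VR).** "This design enables examination of the specific contribution of vigorous physical exertion to the observed outcomes while controlling for VR immersion and digital engagement".
- **Discussion, opening paragraph.** The design is said to allow a secondary exploration of whether benefits come from exertion, from VR engagement or from the two interacting.

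The arms are described as follows. Participants are "allocated 1:1 to an HIIT-based VR exergame intervention (Move Sapiens) or an active control condition". The HIIT arm strikes a drone, avoids its attacks and keeps adjusting its movements; of these mechanics the article says: "This design integrates rapid motor execution, sustained attention, inhibitory control, and visuomotor coordination". The control version "preserves the same immersive VR environment, visual assets, and sound design but removes all components of physical exertion", and "Interaction occurs exclusively through a joystick". Session length and frequency are the same in both arms.

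The limitations paragraph of the Discussion then says that the arms differ in gross motor demand and task experience as well as in metabolic load, and that these differences "preclude definitive attribution of any observed effects to a single component of the intervention".

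**The concern.** Separating exertion from the gaming and VR features of an exergame is the gap that the abstract's Background and the Introduction say earlier trials left open and that this trial sets out to address. What the design can say about exertion is therefore central to the trial's rationale.

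The active control does hold the VR setting constant, which a passive control would not. It does not vary exertion alone: the mode of play changes with it. Suppose the HIIT arm does better on parent-rated inattention or on go/no-go commission errors. The between-arm difference would be a valid estimate of the effect of one package over another. Reporting it as evidence that vigorous exertion is the essential ingredient would be a causal conclusion that the randomisation does not support. A reader of the abstract alone would not meet the caveat that the limitations paragraph gives.

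**Working it through.** The article gives no figure for this claim, so there is none to reproduce. The check compares what the arms contain with what is claimed.

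**Step 1. What differs between the arms**

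| Feature | HIIT arm | Control arm | Source |
|---|---|---|---|
| VR environment, visuals, sound | present | present | Control Condition |
| Session length and frequency | as scheduled | the same | Control Condition |
| Vigorous exertion | present | removed | Intervention Group; Control Condition |
| Full-body movement | present | joystick only | Control Condition; Discussion, limitations |
| Task experience | striking, avoiding, adjusting | differs | Intervention Group; Discussion, limitations |

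Three features change together: exertion (E), gross motor demand (M) and task experience (T).

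**Step 2. What the contrast estimates**

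With VR present in both arms:

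HIIT mean minus control mean = effect of E + effect of M + effect of T + any interactions among E, M and T.

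This is one equation with at least three unknowns. The effect of E cannot be solved from it, whatever the sample size.

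**Step 3. The interaction named in the Discussion**

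Write Y(e, v) for the mean outcome with exertion e and VR v, each 0 or 1. An exertion-by-VR interaction is

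[Y(1,1) − Y(0,1)] − [Y(1,0) − Y(0,0)].

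The two arms supply Y(1,1) and Y(0,1), and even that first bracket carries M and T along with E. Nobody is randomised to exercise without VR, Y(1,0), or to neither, Y(0,0). The second bracket has no data, so the interaction is not estimable.

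**Step 4. Whether the stated analysis or measures help**

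Statistical Methods gives a model with group, time and their interaction, which returns the contrast of Step 2. Additional Measures provides heart rate in laboratory sessions and Borg ratings after every session. Relating these to outcome would compare participants by the exertion they reached or reported, which is not randomised and goes with how much they moved.

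**Step 5. Size**

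No figure in the article divides the contrast. For illustration only, take the effect size of 0.50 assumed in Sample Size as the whole difference, ignore interactions, and assume that a share s comes from M and T together. The exertion part is then 0.50 × (1 − s):

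- s = 0: 0.50 × 1 = 0.50
- s = 0.5: 0.50 × 0.5 = 0.25
- s = 1: 0.50 × 0 = 0

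The range follows entirely from the assumed s. It shows that the data of this trial would not narrow it; it is not an estimate of bias.

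**The case against.** The strongest defence is that the article is more careful than a quick reading suggests.

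- The abstract says only that "The design will enable examination of whether vigorous physical exertion beyond VR immersion and digital engagement constitutes an essential active component", which poses a question and does not announce an answer. A reader might infer that the article claims a between-arm difference isolates exertion. No sentence says so.
- The limitations paragraph names the confounding openly and rules out only definitive attribution. Examining a contribution while declining to attribute it definitively is coherent, so a reader who sees a flat contradiction goes too far.
- The Discussion ranks the question of drivers as secondary, and its closing section reads a positive result as support for the efficacy of the exergame. That is already the package reading.

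Two further inferences are tempting, and the documents do not support them. One is that the control lacks response-inhibition demands, so that a go/no-go advantage could be a practice effect. The article says that exertion was removed and that task experience differs; it does not say whether the adapted version keeps those demands. The other is that the control should have kept whole-body play at lower intensity. That would answer a different question, since the primary objective sets VR without physical exertion as the comparator.

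These points limit the finding but do not remove it. Even put as a question, whether exertion is essential is one that this design cannot answer, and the reference to an interaction has no contrast behind it. A caveat in the limitations does not qualify the abstract or the Methods, where the statements stand without it.

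**Conclusion.** The point holds as a mismatch between stated inference and design. The abstract's conclusions and the control-condition section give a two-arm trial a capability that it lacks, and the opening of the Discussion adds an interaction that cannot be estimated when both arms receive VR. All three are in unreconciled tension with the limitations paragraph.

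The consequence is confined to how a positive result is interpreted. The randomised efficacy comparison in the primary objective, the analysis model, the data and the sample size are unaffected. The conclusion rests on the arms being as the article describes them and on there being no further randomised arm; it needs no assumption about effect size, variance or dropout.

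**What to change.** 1. In the abstract's conclusions, the control-condition section and the opening of the Discussion, state that the randomised contrast estimates the effect of the full-body HIIT VR exergame, as a package, over joystick-operated VR. This agrees with how the closing section of the Discussion already reads a positive result.
2. Remove the description of exertion as an essential active component, the reference to its specific contribution, and the mention of an interaction with VR engagement.
3. Carry the caveat from the limitations paragraph into the abstract's conclusions: the arms also differ in gross motor demand and task experience.
4. Label any attribution to exertion, for example through Borg ratings or laboratory heart rate, as exploratory and nonrandomised.

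The cost is a less strong causal claim; arms, data collection and sample size stay as they are. There is still time: the article expects data collection to run to October 2026 and keeps the final dataset locked until the analysis plan is settled, so the interpretation can be fixed before results are known.

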**Trial Registration:**

ClinicalTrials.gov NCT06632249; https://clinicaltrials.gov/study/NCT06632249

**International Registered Report Identifier (IRRID):**

DERR1-10.2196/94797

## Introduction

Attention-deficit/hyperactivity disorder (ADHD) is a prevalent neurodevelopmental condition that affects approximately 7% of children and adolescents worldwide and is associated with substantial academic, social, and functional impairment that often persists into adulthood [1,2]. Pharmacotherapy, particularly psychostimulants, remains a mainstay of treatment and is effective in reducing core symptoms [3,4]. However, functional impairments frequently persist, long-term academic and psychosocial benefits remain debated, and clinical utility is often limited by adverse effects and poor adherence during adolescence [3,5]. These limitations highlight the need for effective nonpharmacological interventions.

Physical exercise has emerged as a promising adjunctive strategy for youth with ADHD [6]. There is evidence suggesting that exercise interventions can improve specific executive function domains, particularly inhibitory control, as well as core symptoms such as inattention [7]. Nevertheless, adherence to high-intensity exercise protocols is often challenging, especially in adolescents, due to monotony and physical discomfort associated with vigorous exertion [8]. Exergaming, which integrates physical exercise with immersive digital environments, has been proposed as a means of combining physiological stimulation with enhanced engagement and motivation [9,10]. Virtual reality (VR)–based exergames in particular allow for the delivery of structured exercise protocols while maintaining high levels of user involvement.

Despite this potential, a key methodological limitation in the current literature is the difficulty of disentangling cognitive and behavioral effects attributable to physiological exertion from those related to the cognitive and motivational features of gaming and VR environments [9]. Many previous studies have relied on passive or nonequivalent control conditions, limiting causal inference regarding the specific contribution of exercise intensity [7].

To address this gap, this randomized clinical trial evaluates the effects of a high-intensity interval training (HIIT)–based VR exergame compared with an active, nonexercise VR control condition in adolescents with ADHD. The primary objective is to determine whether the HIIT-based VR intervention leads to greater improvements in inhibitory control and inattention than VR exposure without physical exertion.

## Methods

### Study Design and Setting

This study is designed as a multisite, parallel-group, single-blind randomized clinical trial with a 1:1 allocation ratio reported in accordance with the SPIRIT (Standard Protocol Items: Recommendations for Interventional Trials) 2025 guidelines (version 1.0; March 2026). The trial aims to demonstrate the superiority of the active intervention over the control condition. We will collect data at 2 research centers in Brazil: Hospital de Clínicas de Porto Alegre (Rio Grande do Sul) and Centro Escola de Especialidades Médicas in Indaiatuba (São Paulo).

### Ethical Considerations

The protocol has been approved by the ethics committee of the Hospital de Clínicas de Porto Alegre (76899123.1.0000.5327) and adheres to the Declaration of Helsinki and Brazilian General Data Protection Law. Any amendments to this protocol will be submitted to the ethics committee for approval and updated in the trial registry prior to implementation. No formal patient or public involvement was incorporated into the design of this trial. Written informed consent is obtained from legal guardians, and assent is obtained from adolescents prior to any diagnostic assessment. Participants are eligible for an incentive upon study completion: the 3 participants with the highest in-game performance scores across the intervention period will receive a license of EndeavorRx (Endeavor Digital Health).

### Participants and Eligibility

We aim to recruit 98 adolescents using social media advertising, referrals from outpatient ADHD clinics, and institutional databases. Recruitment will be balanced across the 2 study sites.

#### Eligibility Criteria

We will include participants aged 12 to 17 years with a confirmed diagnosis of ADHD according to the Diagnostic and Statistical Manual of Mental Disorders, Fifth Edition. Additionally, participants must demonstrate a score of 12 or higher on the Swanson, Nolan, and Pelham Rating Scale version IV inattention subscale. Regarding medication status, we will include participants who are either medication naive or not currently using ADHD medication (having discontinued use prior to study enrollment for at least 30 days). Importantly, the study does not request or encourage the discontinuation of prescribed medication for research purposes. However, participants who initiate or resume pharmacological treatment during the study period for clinical reasons will be withdrawn from the study to avoid confounding effects.

#### Exclusion Criteria

We will exclude adolescents who present with (1) an estimated IQ below 70; (2) a history of epilepsy, photosensitive seizures, or other neurological conditions incompatible with VR exposure; (3) medical, sensory, or motor limitations that contraindicate HIIT; or (4) severe psychiatric comorbidities, such as active psychosis or major depressive episodes with suicidal ideation. Furthermore, lack of access to a smartphone or reliable internet connection for remote monitoring or engagement in vigorous physical activity more than twice per week will result in exclusion.

### Interventions

#### Intervention Group (HIIT-Based VR Exergame)

Participants allocated to the intervention arm will engage with Move Sapiens, a VR exergame developed using Unreal Engine (version 4.27; Epic Games) and delivered through the stand-alone Meta Quest 2 and 3S headsets (Reality Labs). The game provides a fully immersive, first-person experience where players operate a virtual exoskeleton to combat an autonomous drone. The mechanics require users to simultaneously strike the drone to deplete its health, avoid incoming attacks, and continuously adjust their motor responses. This design integrates rapid motor execution, sustained attention, inhibitory control, and visuomotor coordination. The protocol consists of 20 sessions delivered over a 4-week period (5 sessions per week). Each session lasts 7 minutes and 12 seconds, adhering to a structured HIIT format composed of 12 cycles. Each cycle comprises 16 seconds of maximal physical effort followed by 20 seconds of active recovery. This specific HIIT configuration was previously validated in a pilot crossover study [11]. Results demonstrated that this protocol elicits vigorous physiological responses (mean heart rate of approximately 161 beats per minute; peak heart rate of approximately 182 beats per minute) and significant metabolic stress (lactate accumulation) while maintaining high levels of intrinsic motivation and enjoyment, supporting its utility as a potent physiological stimulus. The structure and visual interface of the Move Sapiens VR exergame are illustrated in Figure 1.

